### Assessment of implementation outcomes and barriers/facilitators to EUC, SPI, and TCBT-S implementation using the RE-AIM evaluation framework

We will embed a strong evaluation of the implementation context for the SPI and TCBT-S interventions. We will utilize two dominant frameworks in implementation science: (1) the RE-AIM evaluation framework [37] to examine implementation outcomes that impact the potential population-health impact of the SPI and TCBT-S interventions; and (2) the Consolidated Framework for Implementation Research (CFIR) determinant framework [38, 39] to systematically assess barriers and facilitators to implementation of the SPI and TCBT-S interventions. Our overall approach will follow a sequential QUAN- > qual explanatory analyses [52] whereby the CFIR framework will be used to help understand results found through our RE-AIM analyses. For example, if we find higher drop-out rates in one arm versus another or find specific schools or individuals with exceptionally positive or negative outcomes we can utilize CFIR focus groups and in-depth interviews to help explain determinants of these outcomes. Together, this rigorous evaluation aims to provide qualitative explanatory contextual models for differences in quantitative implementation outcomes across schools and groups of students. By identifying these barriers and facilitators to implementation, this aim will inform implementation and scale-up strategies for SPI and TCBT-S in Mozambique and other LMICs.

RE-AIM implementation outcomes will be collected throughout trial implementation, summarized at the cluster (school) level, and examined separately across the EUC, SPI alone, and TCBT-S arms; (see Fig. 4). Student-level data will be collected electronically in CommCare [49] alongside primary outcome data during enrollment and intervention administration [47].

**Fig. 4 Fig4:**
[figure not shown]
Proposed RE-AIM indicators for implementation outcome evaluation

Reach analyses will describe youth participation and completion rates and the characteristics of youth reached compared to those not reached. We will utilize sociodemographic characteristics of the planned Mozambique Demographic and Health Survey (2022/3) [53] to compare the representativeness of enrolled youth to the overall population of youth in Sofala Province. We will also examine sociodemographic characteristics of youth who complete intervention activities versus those who drop out or are lost to follow-up.

Effectiveness endpoints will be assessed as described in study outcomes and primary statistical analyses sections.

Adoption will examine the proportion and characteristics of non-specialized health workers and staff who complete training and implement trial activities with at least one youth across arms as well as the proportion and characteristics of schools who agree to participate, uptake, and complete all intervention activities.

Implementation characteristics will include fidelity assessment across the three arms, overall visit completion and contact hours between implementation staff and youth in schools, and cost per participant and primary and secondary outcome by arm.

Fidelity for the SPI arm will be measured using the Safety Plan Intervention Rating Scale for Mozambique (SPIRS-MZ). The SPIRS scale [44] has been used in various contexts, including Mozambique, to certify providers after training in SPI and to monitor fidelity to core intervention elements. SPI fidelity will be assessed by Drs. [name] and [name] through a sample of audio recordings of non-specialist workers administering the intervention. Fidelity monitoring for TCBT-S will include methods successfully used in previous CETA and CBT-based RCTs and following expert approaches for fidelity monitoring in community-based settings [54]. Both provider adherence (completion of required treatment components) and competence (degree of skill) in delivering TCBT-S will be monitored and systematically rated by [name]. [name] will review documentation of sessions to monitor adherence and observe a subset of recorded TCBT-S sessions representing the full range of clinical elements to rate clinical adherence and competence. As is routine during CETA-MZ implementation, [name] will review cases with providers and provide feedback on protocol adherence and competence during weekly supervision. Low adherence or competence will result in additional supervision and training for both SPI and TCBT-S. Fidelity for the EUC arm will include detailed monitoring of appropriate referrals to routine government services (emergency, psychiatric, psychological).

Maintenance will include assessment of extended clinical effects on primary and secondary outcomes through re-administration of assessment tools at 12- and 24-months post enrollment as well as proportion and characteristics of youth retained out to 12 and 24 months.

### Qualitative data collection and analyses

Following quantitative RE-AIM analyses, we will next conduct an explanatory qualitative analysis to determine the innovation, individual, inner setting, outer setting, and processes that distinguish between high- and low-performing schools and youth in each arm. These analyses will be guided by selected CFIR constructs in each domain chosen based on preliminary implementation experience with SPI and CETA-MZ in Mozambique (Table 5) although additional constructs may be included as novel relevant findings emerge throughout the project. Some constructs such as structural characteristics and cost will be covered through quantitative data collection [55]. To conduct these analyses, after we have 6 month primary outcome data, schools in each arm will be rank-ordered on magnitude of clinical effectiveness and we will select the 2 highest and 2 lowest ranking clusters in each arm (12 schools total). We will also examine other RE-AIM indicator performance (with the exception of maintenance) prior to selection to consider inclusion of additional clusters based on those indicators (e.g. clusters with very high or very low participation rates/visit completion). In selected clusters we will also rank-order and examine effectiveness and participation rates of individual students.

**Table 5 Tab5:** Constructs of interest from the Consolidated Framework for Implementation Research (CFIR)

**I. INNOVATION**	
Innovation Source	1
Evidence Base	1
Relative Advantage	1
Adaptability	1
Trialability	1
Complexity	1
Design	1
Cost	2
**II. OUTER SETTING**	
Critical Incidents	1
Local Attitudes	1
Local Conditions	1
External Pressure	1
**III. INNER SETTING**	
Structural Characteristics	2
Culture	1
Compatibility	1
Mission Alignment	1
Available Resources	1
Access to Knowledge	1
**IV. INDIVIDUALS**	
Opinion Leaders	1
Innovation Deliverers	1
Innovation Recipients	1
High/Mid-level Leaders	1
Implementation Team	1
**V. PROCESS**	
Assessing Needs	1
Assessing Context	1
Tailoring Strategies	1
Engaging	1
Adapting	1

1 = qualitative data collection

2 = quantitative data collection

Subsequently, we will conduct 12 focus group discussions (FGDs) among high- and low-performing schools (anticipated 5–10 youth per FGD) and an anticipated 15 in-depth interviews (IDIs) with individual high or low-responding youth. These IDIs will allow for exploration of more sensitive topics and individual perceptions not easily expressed by youth in FGDs. In addition, IDIs will be informed by key themes emerging during FGDs and collect additional target information on emerging themes. If FGDs are deemed not feasible due to sensitivity of youth discussing suicide-related behavior in group format, we will conduct all IDIs. We will also conduct IDIs with a subset of non-specialist healthcare workers supporting the implementation of EUC, SPI, or TCBT-S (anticipated 15 workers). Last, at the end of the final maintenance phase (24 months post enrollment) we will conduct an additional 15 IDIs with youth to examine determinants of exemplary clinical sustainment or activation of key mechanisms.

IDIs and FGDs will be conducted in Portuguese by an experienced facilitator accompanied by a note-taker, audio-recorded, and transcribed verbatim into Portuguese by trained Mozambican staff. Using existing CFIR codebooks as a guide [55], two researchers will use a stepwise, iterative process to review transcripts and identify key deductive themes (using select CFIR constructs, RE-AIM outcomes) while allowing for flexibility of emergent inductive themes. Following iterative coding of transcripts, the trained Mozambican coding team will convene with the PI ([name]) to identify coding discrepancies and assess inter-coder agreement [56, 57]. Once consensus has been reached, two researchers will code all transcripts, and final measures of inter-coder agreement will be conducted (Cohen’s kappa) [58]. If final kappa measurements fall below 0.80, additional reviews of codes will be conducted, and the process will be repeated until agreement is achieved.

### SPI/TCBT-S mechanisms assessment approach

Building on existing published theoretical models of SPI and TCBT-S [30, 59], ongoing studies examining mechanisms of effects [60–62], as well as recent reviews [63] proposing mechanisms of action for SPI and cognitive behavioral interventions for suicide prevention [64] we have specified an intervention-mechanism-outcome conceptual model including six hypothesized mechanisms of action for effects of SPI alone and TCBT-S (see Fig. 5). Utilizing mechanism outcome data collected at intake and longitudinally we will test effects of hypothesized mechanisms and moderators using longitudinal structural equation modeling. Hypothesized mechanisms, preconditions, and moderators will be collected at intake and each effectiveness outcome measurement (3, 6, 12, and 24 months). Table 6 summarizes use of validated measurement approaches [65–70] (where available) to be used for each mechanism. To facilitate feasibility of measurement across numerous mechanisms scales, our team adapted questions from otherwise validated measures (Table 6), selecting questions with high factor loadings from applicable constructs. Primary analyses of mechanisms will occur at the end of the primary effectiveness outcome (6 months). Secondary analyses will occur at the end of the maintenance phase (24 months).

**Fig. 5 Fig5:**
[figure not shown]
Causal pathway model of hypothesized mechanisms of SPI and TCBT-S effects

**Table 6 Tab6:** Variable definitions for mechanistic structural equation model

Construct	Measurement Approach
***Moderators***	
Patient engagement	Study Visit Reports
Sex	Study Enrollment Form
Age	Study Enrollment Form
Baseline Suicide Risk	Columbia Suicide Severity Rating Scale (C-SSRS)
Depressive Symptoms	Patient Health Questionnaire (PHQ-9-MZ)
***Mechanisms***	
Cognitive Reappraisal	Emotion Regulation Questionnaire for Children and Adolescents (ERQ-CA)
Cognitive Flexibility	Cognitive Flexibility Inventory (CFI)
Suicide Related Coping	Suicide Related Coping Scale (SRCS)
Increasing Connection	EPOCH Measure of Adolescent Well-Being, connectedness subscale
Self-efficacy	General Self-efficacy Scale (GSES)
Emotional Regulation	The Difficulties in Emotion Regulation Scale—Short Form (DERS-SF)
Increasing Difficulty of Suicidal Behavior	Study specific questionnaire

### SPI/TCBT-S mechanisms assessment power

Overall, this study was powered to test the effectiveness of SPI or TCBT-S to decrease odds of suicidal behavior in the past month. Given the lack of previous research on mechanisms for SPI and CBT-based interventions for suicide prevention in the African context, this aim will focus on an exhaustive examination in search of practically- and clinically meaningful mechanism and moderator effect estimates for further examination in subsequent research. The goal of this aim is to contribute to theory building to inform future studies specifically powered to test hypothesized causal pathway models. No confirmatory hypothesis testing driven by p-value inference will be performed, as recommended when conducting exploratory studies by Leon (2011) [71]. However, we will have a sufficient sample size to have stable effect estimates with reasonable precision based on our design including a baseline measurement and 4 follow-up measurements among a minimum of 100 youth across 21 schools (10,500 observations total).

### SPI/TCBT-S mechanisms assessment analyses

Our analytical plan will progress in 3 stages. First, we will conduct univariate examination of hypothesized mechanism effects using multi-level longitudinal SEM accounting for multiple students nested within schools across time. The purpose of this will be to examine single main effect estimates for hypothesized mechanisms. For example, we will estimate a univariate multi-level longitudinal SEM of both SPI and TCBT-S intervention effects predicting increased social connectedness then increased connectedness predicting decreased suicidal behavior (dashed line in Fig. 5). We will conduct diagnostics, including assessing linearity of mechanism effects, model residual distributions, and variance accounted for in mechanisms and outcomes. We will then test potential moderators in univariate models, in search of those that strongly affect strength or direction of univariate effects. Moderators will be examined for their effect on intervention activation of mechanisms (left side of Fig. 5) as well as mechanism effects on suicidal behavior (right side of Fig. 5). Second, we will include all mechanisms simultaneously in a multivariable longitudinal multi-level SEM. Including all mechanisms, even those showing no effects in univariate models accounts for potential suppressor effects [72]. Moderators that showed meaningful effects in univariate models will then be included in a final multivariable model. Final model diagnostics will be verified, and variance accounted for in mechanisms, as well as outcomes, will be reported. This multivariable model will allow examination of: (1) mechanisms most affected by SPI and TCBT-S interventions (left side Fig. 5); (2) mechanisms that influenced outcomes (right side Fig. 5); and (3) the product of #1 and #2 path coefficients indicating the indirect effect of SPI or TCBT-S on treatment outcomes operating through a given mechanism. Separating paths #1 and #2 can inform intervention improvements; for example, if a mechanism had a large effect on outcomes (path #2) but was only weakly activated by the SPI intervention (path #1), the intervention could be modified to enhance activation of this potentially high-leverage mechanism.

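### The only stated route for baseline suicide risk, depression, age and sex into the final mechanism model is a moderation screen, which leaves the mechanism-to-outcome path open to foreseeable confounding

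*Protocol article*

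**What the plan says.** Table 6 of the protocol article lists five variables as moderators: patient engagement, sex, age, "Baseline Suicide Risk" (C-SSRS) and "Depressive Symptoms" (PHQ-9-MZ). It gives them no other role.

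The section *SPI/TCBT-S mechanisms assessment analyses* describes what happens to them. In the first stage: "We will then test potential moderators in univariate models, in search of those that strongly affect strength or direction of univariate effects". In the final stage: "Moderators that showed meaningful effects in univariate models will then be included in a final multivariable model".

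Mechanisms are treated differently. All of them enter the multivariable model whatever their univariate result: "Including all mechanisms, even those showing no effects in univariate models accounts for potential suppressor effects".

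The final model then yields path #1 (intervention to mechanism), path #2 (mechanism to outcome) and "the product of #1 and #2 path coefficients indicating the indirect effect of SPI or TCBT-S on treatment outcomes operating through a given mechanism". As an example of use, if a mechanism has a large path #2 but is weakly activated, "the intervention could be modified to enhance activation of this potentially high-leverage mechanism".

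The intake values are available. *SPI/TCBT-S mechanisms assessment approach* says: "Hypothesized mechanisms, preconditions, and moderators will be collected at intake and each effectiveness outcome measurement (3, 6, 12, and 24 months".

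**The concern.** Schools are randomised to arms, and this protects path #1. Nobody is randomised to a level of coping, self-efficacy or connectedness, so path #2 is an observational association among youth. It needs control of the common causes of mechanism score and later suicidal behaviour. Baseline suicide risk, depression, age and sex are the natural candidates.

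The stated screen asks a different question: does the variable change the strength or direction of an effect? A strong common cause with no interaction fails that screen. Any mechanism score that runs lower in more severely affected youth would then look protective, even if changing it did nothing.

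The authors keep every mechanism because univariate results can mislead. The same caution is not applied to the likeliest confounders. At stake is which mechanisms the aim passes on to later studies as worth targeting.

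**Working it through.** **1. The plan's own figure.** *SPI/TCBT-S mechanisms assessment power* gives 10,500 observations: 21 schools × 100 youth × 5 measurements = 10,500. It reproduces. A sample of this size gives precision but does not reduce bias.

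**2. Benchmark.** *Primary study power assessment* assumes 37% against 24% with suicidal behaviour. On the log-odds scale this is ln(0.24/0.76) − ln(0.37/0.63) = −1.153 + 0.532 = −0.62.

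**3. Other routes to adjustment.** *Primary statistical analyses* says that age, sex, grade, school size and school location will be considered according to balance. That covers the effectiveness models. It omits baseline suicide risk and depression, and balance between arms does not bear on path #2. The mechanism sections state no main-effect adjustment.

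**4. Simple simulation** (400,000 youth per cell, one time point, one mechanism, no clustering). Severity U is standard normal. M = −rU + noise, with unit variance. logit P(Y) = −0.55 + gU, which puts prevalence near 37%. The true effect of M is 0. The values of r and g are assumptions. The last column takes an assumed 0.3 SD intervention effect on M: 0.3 × path #2 / (−0.62).

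| r | g | path #2 without U | OR per SD | false indirect effect / −0.62 |
|---|---|---|---|---|
| 0.3 | 0.5 | −0.146 | 0.86 | 7% |
| 0.4 | 0.7 | −0.264 | 0.77 | 13% |
| 0.5 | 1.0 | −0.435 | 0.65 | 21% |

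With U entered, path #2 is about 0 (OR about 1.00) in every row.

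**5. Simulation at trial size** (300 replicates per cell, 2,100 youth, 21 schools, three arms, outcome rate near 37%, ICC 0.02). An intake variable C affects M and Y with no interaction. M is inert and is raised 0.4 by treatment. The correlation of C with intake M and the log-odds slope of C are again assumptions.

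| correlation | slope | path #2 without C | 95% interval excludes 0 | false indirect effect |
|---|---|---|---|---|
| 0 | 0.3, 0.6 | 0.002, 0.005 | 6% | 0.001, 0.002 |
| −0.2 | 0.3 | −0.062 | 27% | −0.025 |
| −0.2 | 0.6 | −0.114 | 67% | −0.046 |
| −0.4 | 0.3 | −0.113 | 69% | −0.046 |
| −0.4 | 0.6 | −0.221 | 99.7% | −0.088 |

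In the weakest biased cell the SD of M is 0.976, so the OR per SD is exp(−0.062 × 0.976) = 0.94. The false indirect effects are 0.025/0.62 = 4% to 0.088/0.62 = 14% of the benchmark.

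- **C always entered:** path #2 is 0.001 to 0.008, and the interval excludes 0 in 4% to 8% of replicates.
- **Intake mechanism and intake outcome entered, but not C:** in the biased cells path #2 is −0.04 to −0.13, and the interval excludes 0 in 13% to 65%. At a lift of 0.4 the false indirect effect is 0.4 × 0.039/0.62 = 3% to 0.4 × 0.127/0.62 = 8% of the benchmark.
- **Would the screen admit C?** An M × C interaction test at an assumed threshold of p < 0.05 admits it in 4% to 7% of replicates, about the chance rate.

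**The case against.** **The text does not exclude these variables.** A reader might infer that the plan bars them unless they moderate. The article does not say so. Its sentence tells us which moderators are carried forward, and a condensed article may leave a covariate list to the analysis plan. Fig. 5, the causal pathway model, is not visible, and the article mentions preconditions that the visible part of Table 6 does not list. This stands, and it limits the point to the only *stated* route. The article does still state a selection rule for these particular variables, and the rule selects on the wrong property.

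**The screen's wording is loose.** No threshold is given, and a variable whose entry shifts the mechanism coefficient might arguably qualify. Moderation is the more natural reading, but the 4% to 7% admission rate depends on an assumed test.

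**The simulations are simpler than the plan.** The plan is a multilevel longitudinal structural equation model with all mechanisms together. Correlated mechanisms may absorb part of the severity effect, and enrolling only youth with active ideation may narrow the range of severity. This stands as a limit on size. Adjusting for intake mechanism and outcome reduced the bias but did not remove it, and the article does not specify even that adjustment.

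**The aim is exploratory.** It is declared as theory building without p-value inference, and changing the intervention is offered only as an example. This limits the consequence. Leaving out p-values does not make a biased path estimate unbiased.

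**Conclusion.** The point holds as a weakness in a stated rule. A moderation screen is the only route the article gives by which sex, age, baseline suicide risk and depressive symptoms enter the final mechanism model. A non-interacting common cause would not be carried forward, so path #2 and the indirect effect are open to foreseeable bias.

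The size rests on assumed correlations and slopes. Over correlations of −0.2 to −0.5 and slopes of 0.3 to 1.0, an inert mechanism shows an odds ratio of about 0.94 to 0.65 per SD in a single-time-point model. It shows less if intake mechanism and outcome are modelled, and none at zero correlation.

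Two stronger readings are not supported. One is that path #2 *is* confounded: that depends on associations that the article does not quantify. The other is that the trial's findings are at risk: the primary and secondary effectiveness analyses do not use this model. Table 6 also does not label depressive symptoms as an intake measure, although intake values are collected.

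**What to change.** In *SPI/TCBT-S mechanisms assessment analyses*:

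- Enter intake C-SSRS risk and suicidal behaviour, intake PHQ-9-MZ, age, sex and each mechanism's intake value as main effects in the mechanism and outcome equations. Do this in all univariate and multivariable models, whether or not the variable moderates.
- Keep the meaningful-effects rule for adding interaction terms only.
- State that path #2 remains open to unmeasured confounding. The simulated return to 1.00 occurs because the simulation has a single, measured confounder.

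The cost is a change of wording and a few more parameters per model. The article already plans to collect these variables at intake.

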### Study outcomes

Primary study outcomes will be youth-level suicidal behavior in the past month (primary), suicidal ideation in the past month (secondary), depressive symptoms in the past 2 weeks (secondary); (Table 3). Suicidal behavior was selected as the primary trial outcome due to previous meta-analyses showing SPI and CBT interventions for suicide prevention to have the strongest effects on reducing suicidal behavior [14, 17]. In the present trial, all primary and secondary outcomes will be collected at 3-, 6-, 12-, and 24-months post intake. Primary analyses will occur at 6 months following the strongest evidence from previous trials. Secondary outcomes of suicidal ideation and depressive symptoms are included due to mixed evidence on these outcomes from CBT-based suicide prevention meta-analyses [16, 17]. The DSM-5 crosscutting assessment and the RCADS-25 youth will also be collected at all timepoints due to requirements imposed by the NIMH Common Data Elements [47]. As shown in Table 3, suicidal behavior will be measured through reported actual suicide attempts, interrupted attempts, aborted attempts, or specific preparatory acts or behavior reported on the C-SSRS for youth [40, 41]. Our team has previously translated, adapted, and applied the C-SSRS to evaluate suicidal behavior among youth in schools in Mozambique and the instrument was acceptable, appropriate, and feasible to implement [13]. Suicidal ideation will include active suicidal thoughts reported in the past month on the C-SSRS. Clinically-significant depressive symptoms will be measured through the PHQ-9-MZ, a Mozambique adaptation of the PHQ-9 that our team has previously validated for use in Sofala, Mozambique [48]. Patient-level data collection will be done in CommCare [49], which our team is currently using for longitudinal patient tracking for a mental health cRCT in Sofala Mozambique [47]. All data will be stored on encrypted and password protected computers, accessible only to the named study staff. Any identifying features needed to link follow-up of patients over time will be destroyed at the end of the 24-month follow-up period.

**Table 3 Tab3:** Primary and secondary clinical outcome indicators and definitions

Outcome	Indicator	Definition
PRIMARY	Suicidal behavior in past month	Actual suicide attempt, interrupted attempt, aborted attempt, or specific preparatory acts or behavior reported on the C-SSRS in past month

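### The mechanism plan reads one product of path coefficients as the indirect effect from a model that keeps moderators of those paths; once a moderator is retained, a single product no longer describes the indirect effect in the trial population

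*Protocol article*

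**What the plan says.** The section *SPI/TCBT-S mechanisms assessment analyses* of the protocol article sets out the following sequence.

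- Candidate moderators are tested in single-mechanism models, "in search of those that strongly affect strength or direction of univariate effects". They are examined on both sides of Fig. 5: activation of the mechanism by the intervention (path #1), and the mechanism's effect on suicidal behavior (path #2).
- All mechanisms are then entered together, after which "Moderators that showed meaningful effects in univariate models will then be included in a final multivariable model".
- The outputs are listed next: "This multivariable model will allow examination of: (1) mechanisms most affected by SPI and TCBT-S interventions", then the mechanisms that influenced outcomes, and as item (3) "the product of #1 and #2 path coefficients indicating the indirect effect of SPI or TCBT-S on treatment outcomes operating through a given mechanism".

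Table 6 lists the candidate moderators: patient engagement, sex, age, baseline suicide risk and depressive symptoms. The section on mechanism power describes the aim as exploratory, without confirmatory p-value inference, and directed at meaningful mechanism and moderator effect estimates.

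**The concern.** Item (3) names one product per arm and mechanism as the indirect effect. The model that supplies it contains moderators kept because they change the strength or direction of the paths being multiplied. When the screen finds nothing, the rule works. When it finds a moderator, there is no longer one indirect effect, and the article does not say which value the single product stands for.

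This matters because the aim sets p-values aside, so the estimates are its whole output. The Discussion expects the mechanistic results to guide optimization and tailoring of SPI and TCBT-S. A product that reflects one reference subgroup could misstate how much of an arm's effect runs through a mechanism. It could also hide that the mechanism works in one group and not, or in the opposite direction, in another.

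**Working it through.** **The plan's own figure.** The only number given for this aim is the observation count: (1 baseline + 4 follow-ups) x 100 youth x 21 schools = 10,500. It reproduces exactly and is not in dispute.

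**Formula.** Let w be a retained moderator, with path #1 = a0 + a1\*w and path #2 = b0 + b1\*w on a linear scale.

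- Indirect effect at w: (a0 + a1\*w)(b0 + b1\*w).
- This equals a0\*b0 at every w, whatever the main paths are, only if a1 = b1 = 0.
- Otherwise a0\*b0 is the indirect effect at w = 0 on the coded scale.
- Population average = product of the paths at the mean of w, plus a1\*b1\*Var(w).

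**Inputs.** The article gives no path values, so all of those below are assumptions. The moderator is sex, coded 0/1 and split 50/50, so Var(w) = 0.25.

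| Case | Path #1, w=0 / w=1 | Path #2, w=0 / w=1 | Effect at w=0 | Effect at w=1 | Average | Product after centring |
|---|---|---|---|---|---|---|
| A. No moderation | 0.4 / 0.4 | -0.5 / -0.5 | -0.20 | -0.20 | -0.20 | -0.20 |
| B. Path #1 weaker | 0.4 / 0.1 | -0.5 / -0.5 | -0.20 | -0.05 | -0.125 | -0.125 |
| C. Path #1 reversed | 0.4 / -0.2 | -0.5 / -0.5 | -0.20 | +0.10 | -0.05 | -0.05 |
| D. Both moderated | 0.4 / 0.7 | -0.5 / -0.8 | -0.20 | -0.56 | -0.38 | -0.358 |
| E. Both moderated | 0.2 / 0.6 | -0.3 / -0.8 | -0.06 | -0.48 | -0.27 | -0.22 |

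**Reading the table.**

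- In cases A to D the product of main coefficients is the same, -0.20, while the average runs from -0.05 to -0.38.
- In case E, recoding sex changes the product from 0.2 x (-0.3) = -0.06 to 0.6 x (-0.8) = -0.48, an eightfold change with the same data.
- Centring recovers the average when one path is moderated (B, C), but in case C the single value of -0.05 hides effects of opposite sign.
- Centring does not recover the average when both paths are moderated. In case E the centred product is 0.4 x (-0.55) = -0.22. The missing term is a1\*b1\*Var(w) = 0.4 x (-0.5) x 0.25 = -0.05, and -0.22 - 0.05 = -0.27.

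**The case against.** The strongest reply is that a product of paths is the generic definition of an indirect effect, and that in a moderated model the paths are understood as conditional. A condensed article may leave coding, centring and the reporting of conditional effects to a fuller plan, so silence on those details is not a fault. That stands. What remains is the rule the article does state: one product, called the indirect effect, read from a model with moderators in it. If conditional paths are meant, there is no single product, and item (3) has to say at which values it is taken or how it is averaged.

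It is also fair to say that the problem arises only if a moderator of the path in question is retained, and that the aim is exploratory.

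Three stronger readings are tempting, and the document does not support them.

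- *The sign will be wrong because the product refers to age zero.* With path #1 at 0.30 at age 16, a slope of 0.05 per year and path #2 at -0.5, uncentred age gives (0.30 - 16 x 0.05) x (-0.5) = +0.25, against -0.15 at age 16. This assumes uncentred age, which the article does not state; centring age at 16 restores -0.15.
- *The product is on the wrong scale for a binary outcome.* The mechanism section names no link for the structural equation model; the logit link in *Primary statistical analyses* belongs to the outcome models. Nor does the article plan to set the product against a risk difference or to split a total effect.
- *Mechanisms will be ranked wrongly by this product.* There is no ranking rule. The article's example of a high-leverage mechanism compares path #1 with path #2 separately and does not use the product.

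**Conclusion.** The point holds in a limited form. As worded, item (3) gives an adequate single summary only when no moderator of the relevant path is retained. If one is retained, the product of main coefficients is the indirect effect at the coded reference value. It changes with the coding and can conceal subgroup differences or reversals, and centring is only a partial remedy when both paths are moderated.

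The size cannot be taken from the article. In the assumed examples the product of -0.20 stands against averages from -0.05 to -0.38, and one pair of moderated paths gives -0.06 or -0.48 by coding alone. These figures rest on linear paths, a binary moderator split evenly, and invented coefficients. They show that the rule can mislead, not that it will.

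The consequence is confined to the exploratory mechanism aim. The primary and secondary outcome results are unaffected.

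**What to change.** Amend item (3) along these lines: *Where a moderator of path #1 or path #2 is retained, the indirect effect for each arm and mechanism will be reported as conditional indirect effects at stated moderator values (each level of a categorical moderator; quartiles of a continuous moderator, centred) and averaged over the observed moderator distribution. Paths #1 and #2 will also be shown by moderator level. Where none is retained, the single product will be reported.*

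If path #2 is fitted with a logit link, it is preferable also to give the effect as a difference in predicted probability of past-month suicidal behavior at 6 months, the time point of the primary mechanism analysis. That sentence must state how the other mechanisms are held and how the random effects are handled, because the predicted probability is not defined without them.

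The cost is some post-estimation code and more estimates to report per mechanism. No new data, sample size change or change to the primary analysis is needed.
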